### Secondary Outcomes

Efficacy endpoints include the following: (1) Eczema Area and Severity Index (EASI) scores (13) at 4, 12, 24, and 32 weeks after birth; (2) patient-oriented eczema measure (POEM) scores (14) during the study; (3) stratum corneum hydration at the date of registration at 4, 12, 24, and 32 weeks after birth; (4) total immunoglobulin E (IgE) antibody titer and specific IgE antibody titer (ImmunoCAP) at the diagnosis of AD or at 32 weeks after birth; and (5) serum thymus and activation-regulated chemokine levels at diagnosis of AD or at 32 weeks after birth (15).

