**ASSESSMENTS**							
Background information	X						
Living environment	X				X		X
Nutrition	X				X		X
Body height	X	X	X	X	X	X	X
Body weight	X	X	X	X	X	X	X
Evaluation of the presence or absence of atopic dermatitis by a blinded physician	X	X	X	X	X	X	X
EASI score by a blinded physician		X	X	X	X		X
POEM score by caregivers		→	→	→	→		→
Stratum corneum hydration	X	X	X	X	X		X
Total IgE, egg white, ovomucoid, milk, wheat, peanut, and *Dermatophagoides farinae*-specific IgE and TARC in serum					X		X
Check the diary		X	X	X	X	X	X
Amount of emollients used		X	X	X	X	X	X
Combination therapy		X	X	X	X	X	X
Adverse events		X	X	X	X	X	X

*EASI, Eczema Area and Severity Index; POEM, patient-oriented eczema measure; TARC, thymus and activation-regulated chemokine; IgE, immunoglobulin E*.

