### Sample Size Calculation

A total of 60 participants, with 20 in each group, will be enrolled in this study. This is an exploratory study, and the target case size was selected based on the research period and available resources (feasibility). In our institute, the number of births exceeds ~2,000 per year, and the number of singletons born at 37 weeks after pregnancy is ~1,200 per year. An epidemiological study of AD in Japan showed that the overall AD prevalence was 6.9%. Moreover, the AD prevalence was 9.8, 8.7, 4.4, and 2.6%, respectively, for those in their 20, 30, 40, and 50/60s. The results showed that AD prevalence was higher in women than in men (9.3 vs. 5.1%) (16). Recently, a Japanese national cohort study showed that maternal AD diagnosis was found in 15.7% of mothers (17). Therefore, recruiting 60 neonates within the 8-month registration period should be possible.

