### Statistical Methods

#### Statistical Methods for Outcomes

Analysis will be performed according to the intention-to-treat principle. To assess whether group A or group B is more effective than group C in preventing the onset of AD, we will use two co-primary analyses using the log-rank test for the time to the onset of AD. The significance level of each comparison is 2.5%. For each group, Kaplan–Meier estimates of the AD-free rate will be determined. Additionally, the Cox proportional hazards model will be used to estimate the hazard ratios of groups A vs. C and groups B vs. C, and their 95% CIs. The CIs will be calculated using the Wald type method. The exact method will be applied to adjust for tied observation times. A test with Schoenfeld residuals will be used to assess the proportional hazard assumption. If a significance level of 10% rejects the validity of the proportional hazards assumption, group comparisons using the difference in the restricted mean survival time will be applied as a supplementary analysis of the co-primary analysis. For the secondary endpoints, the mean and standard deviation of continuous variables, and the frequency and proportion of discrete variables will be calculated for each treatment group and time point. For the safety endpoints, the frequency and proportion of adverse events occurring will be calculated for each treatment group.

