#### Methods for Additional Analyses (e.g., Subgroup Analyses)

We do not plan additional analyses.

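### Mean and SD are the stated summary for total IgE, specific IgE and TARC; if these are right-skewed, that summary is unstable with 20 infants per arm (minor)

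*Protocol article*

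**What the plan says.** Secondary Outcomes in the protocol article lists as efficacy endpoints "total immunoglobulin E (IgE) antibody titer and specific IgE antibody titer (ImmunoCAP) at the diagnosis of AD or at 32 weeks after birth" and "serum thymus and activation-regulated chemokine levels at diagnosis of AD or at 32 weeks after birth". Both are worded as titers or levels, that is, as continuous quantities. The assessment schedule (Table 1) names the analytes: "Total IgE, egg white, ovomucoid, milk, wheat, peanut, and" a house dust mite, plus TARC. That makes one total IgE, six specific IgE and one TARC result per infant, eight in all.

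Statistical Methods for Outcomes then gives a single rule for this class of endpoint: "For the secondary endpoints, the mean and standard deviation of continuous variables, and the frequency and proportion of discrete variables will be calculated", by treatment group and time point. It mentions no log scale, geometric mean, median or quartiles, and no test or between-group contrast for these endpoints. The section on additional analyses states: "We do not plan additional analyses".

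On size: "A total of 60 participants, with 20 in each group, will be enrolled in this study", where "the target case size was selected based on the research period and available resources (feasibility").

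**The concern.** The article names the summary, so this is a stated choice and not a detail left to a document that is not shown. Mean and SD describe roughly symmetric variables well. For a positive, right-skewed variable in a group of 20, a few high values carry much of the mean and even more of the SD. Mean plus or minus SD can then reach below zero for a quantity that cannot be negative.

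A result reported only as below the assay limit has no number to average until a value is substituted, and the substituted value then enters the mean directly.

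What is at stake is how the sensitisation results are read. The Introduction explains the interest in early skin care partly through percutaneous sensitisation and later food allergy. The Discussion cites a pilot trial in which twice-daily moisturizer was linked to less IgE sensitisation. IgE is the only measure of sensitisation collected here, and Confidentiality says the data will be used for phase III. An arm mean raised by one or two infants could be taken as a signal.

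**Working it through.** **Inputs from the article.** 60 infants in three equal arms: 60 / 3 = 20 per arm. The summary is mean and SD. The sample size rests on feasibility, so there is no power figure to reproduce.

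**Inputs assumed.** The article gives no distribution, spread, assay limit or share of results below a limit. I take lognormal values with natural-log SD s = 0.8, 1.2 and 1.6. The corresponding geometric SDs, exp(s), are about 2.2, 3.3 and 5.0.

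**Step 1: SD relative to mean.** For a lognormal variable the population ratio SD / mean is √(exp(s²) − 1).
- s = 0.8: √(1.90 − 1) = 0.95
- s = 1.2: √(4.22 − 1) = 1.79
- s = 1.6: √(12.94 − 1) = 3.45

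So the SD exceeds the mean in the population at the two wider spreads, but not at 0.8.

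**Step 2: arms of 20.** Simulation of 200,000 pairs of arms with the same true distribution. The last two columns give the chance that the two arms differ at least two-fold in either direction.

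| s | Highest infant's share of arm total (median) | SD exceeds mean | Two-fold gap, arithmetic means | Two-fold gap, geometric means |
|---|---|---|---|---|
| 0.8 | 16% | 19% | 1.8% | 0.6% |
| 1.2 | 24% | 76% | 16.4% | 6.7% |
| 1.6 | 32% | 96% | 35.2% | 17.0% |

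With equal values, each infant's share would be 1/20 = 5%.

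The last column has a closed form. The difference of two log means has standard error s × √(2/20), so the chance is 2 × [1 − Φ(ln 2 / (s√0.1))]. At s = 1.2 this is ln 2 / 0.379 = 1.83, giving 6.8%. At s = 1.6 it is 0.693 / 0.506 = 1.37, giving 17.1%. Both agree with the simulation.

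**Step 3: second run over a wider range of spreads.** At geometric SDs of 1.5, 2, 3, 5 and 8:
- the highest infant's median share is 10, 14, 22, 32 and 41%;
- the SD exceeds the mean in 0, 7, 65, 96 and 99% of groups;
- dropping the highest infant lowers the arithmetic mean by 5, 10, 18, 28 and 38%, and the geometric mean by 4, 6, 10, 14 and 18%.

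The share and the fall are consistent: the fall is 1 − (1 − share) × 20/19, which at geometric SD 3 is 1 − 0.78 × 20/19 = 18%.

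**Step 4: results below the limit.** If a proportion q of results lies below the limit, the chance that an arm of 20 has at least one is 1 − (1 − q)^20. This is 1 − 0.9^20 = 0.88 at q = 10%, and 0.999 at q = 30%. With the limit scaled to 1, substituting 0 or the limit itself moves the mean by about q. At geometric SD 3 the median arm means are:
- q = 10%: 6.96 versus 7.06, a negligible difference;
- q = 50%: 1.48 versus 1.96;
- q = 90%: 0.16 versus 1.06. The SD moves the other way, from 0.50 to 0.20.

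Substitution therefore matters only when a large share of results is below the limit.

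**The case against.** The best case for leaving the text alone has four parts.

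**The spread is assumed.** This stands. Nothing in the article shows how skewed these markers will be, one log-SD need not suit total IgE, specific IgE and TARC alike, and at a log-SD of 0.8 or a geometric SD of 2 there is little to correct.

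**Much of the instability comes from the sample size.** This stands in part. Geometric means of identical arms still differ two-fold in 7 to 17% of trials at the wider spreads, and the article says openly that 20 per arm is a feasibility choice for an exploratory study. The arithmetic mean still roughly doubles that chance.

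**Nothing is tested.** This stands. A reader might infer a loss of power from the raw scale, but the plan makes no test or contrast on these endpoints, so power comparisons describe an analysis that does not exist. The stated objective concerns prevention of AD only.

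**Handling of low results and positivity cut-offs may sit in the analysis plan.** This also stands. A reader might infer that the means cannot be derived at all, or that the proportion sensitised will never be reported. The documents support neither. With a substitution rule the mean and SD can be calculated, and the same sentence of the article provides frequencies and proportions for discrete variables, so a cut-off defined elsewhere would fit it.

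What these arguments do not remove is the wording itself: mean and SD are the only summaries the article names for these eight results.

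**Conclusion.** The point holds as a minor, optional improvement. Mean and SD are stated for total IgE, specific IgE and TARC, and they suit these variables poorly if the values are strongly right-skewed. The size depends on the assumed spread: material at a log-SD of 1.2 to 1.6 and small at 0.8.

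It would go too far to say that one infant dominates the means or that they mostly reflect that infant. Even at the wide spreads the median share is 24 to 32%. A share above half is uncommon: at geometric SD 5, one arm in ten reaches 57% or more.

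Dependence on a substituted value is a further weakness for specific IgE, but only if a large share of results is below the limit, which the documents do not say. The two co-primary log-rank comparisons and their error rate are unaffected.

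**What to change.** In Statistical Methods for Outcomes, make an exception for total IgE, specific IgE and TARC:
- Report median and quartiles in place of mean and SD. The geometric mean is an alternative where most values are quantifiable; where many are not, it too depends on the substituted value.
- Give the number of results below the reporting limit in each group.
- For each specific IgE, also report the number and proportion of infants at or above a positivity cut-off fixed before the data are seen.

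If the analysis plan already does this, bringing the article's sentence into line with it is enough. Between-arm ratios or risk differences with confidence intervals are not needed for a plan that only describes these endpoints. The cost is one sentence and a few table shells, with no new samples, visits or infants.

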#### Interim Analyses

We do not plan an interim analysis.

#### Methods for Additional Analyses (e.g., Subgroup Analyses)

We do not plan additional analyses.

#### Methods in Analysis to Handle Protocol Non-adherence and any Statistical Methods to Handle Missing Data

Analysis of the primary and secondary outcomes will be performed on the full analysis set. As a reference, analyses will be performed for each protocol set.

(1) Full analysis set

Among all randomized subjects, the following will be excluded:

Subjects who have never had study interventionSubjects for whom data were not obtained since the start of the study interventionSubjects found to be in violation of eligibility criteria after the fact

(2) Per protocol set

A group of subjects in the full analysis set who do not have significant deviation from the implementation plan will be included. Subjects with the following will be excluded from this group:

Poor adherence (application amount is <70% of the planned application amount during the study intervention period, or the number of days that the correct number of applications can be performed is <70% of the planned application period during the study intervention period)If adherence cannot be evaluatedWhen using bath salts for longer than 7 daysMoisturizer other than the test moisturizer or control moisturizer, skin external medicines, and skin application agents are applied for 7 days or longer (excluding external use only around the mouth, pubic area, and anus)

#### Plans to Provide Access to the Full Protocol, Participant Level-Data, and Statistical Code

We do not plan to provide access to the full protocol, participant level-data, and statistical code.

##### Composition of the Data Monitoring Committee, and Its Role and Reporting Structure

Central and onsite monitoring will be conducted to ensure that this study is conducted safely and according to the research protocol and that data are being collected accurately. Monitoring will be conducted by a person designated by the investigator. The study is independent from the sponsor and competing interests. An independent data monitoring committee will be established in this study to monitor the safety of the study.

##### Frequency and Plans for Auditing Conduct of the Trial

We do not plan auditing in this study.

##### Plans for Communicating Important Protocol Amendments to Relevant Parties (e.g., Trial Participants and Ethical Committees)

After the approved Clinical Research Review Committee at this facility approves a change in the research implementation plan, notification of this change will be submitted to the local welfare department. After approval by the accredited clinical research review board, approval of the administrator of the implementing medical institution regarding the revised content will be obtained. If permission is obtained, the investigators will send a copy of the permit to the Research Secretariat and changes to the research protocol will take effect.

## Discussion

This is the first phase II, three-armed RCT in Japan to estimate how effective the twice daily or once daily application of Fam's Baby moisturizer is for preventing AD compared to the once daily application of 2e moisturizer, which was suggested to have a preventive effect on AD in neonates with a high-risk of developing AD. In this study, we will use 2e once daily as a control moisturizer, which we confirmed as effective for primary prevention of AD in our previous RCT (9). Based on the results of this study, we hope that a phase III study will be conducted to determine the optimal method for preventing AD *via* moisturizer application.

Filaggrin (FLG) mutation carriers have an increased risk of AD (18). Because participants have an AD family history, it is presumed that the rate of participants with FLG mutations is relatively high, and children with FLG mutations may have a higher chance of preventing AD with the use of moisturizers. FLG mutations, this time, are not evaluated because of research costs and feasibility. However, we believe that randomizing participants controls the variation between FLG mutation groups and minimizes the impact on results. In phase III, we would like to evaluate the differences in effect depending on the presence or absence of FLG mutation.

### Other Similar Studies

As mentioned above, our previous RCT provided evidence that protecting the skin barrier with a moisturizer applied at the beginning of the neonatal period prevented development of infantile AD (9). However, prevention of AD was not proven in the study (10) in high-risk neonates in the UK and in the study (11) in general populations of Norway and Sweden. Once daily moisturizer was proposed in the study protocols of these two previous studies (10, 11). Reasons for the inconsistency in results for moisturizer interventions might be due to different countries and cultures, different types of moisturizers, and differences in adherence. Dissanayake et al. (19) performed an RCT in Japan to examine whether combined synbiotics and skin moisturizers could prevent AD and food allergy. However, they did not show efficacy of moisturizer application two to three times/day against prevention of AD and food allergy. The actual amount of moisturizer application and adherence in their study were unclear. Lowe et al. (20) reported that applying a sufficient amount of moisturizer twice daily (≥5 days per week, good adherence) in neonates was preventable for sensitization of IgE at the age of 12 months in a small pilot RCT. We believe that the key points of a strategy for preventing allergies by skin moisturizer are as follows: (1) applying a sufficient amount of moisturizer, (2) twice daily application of moisturizer, and (3) the quality of the moisturizer. An individual patient data meta-analysis is ongoing by an international collaboration group (SCiPAD) to identify whether skin care interventions in infants prevent development of AD and food allergy (21). New evidence for skin care prevention, such as application of moisturizer, will be determined.

### Potential Benefits of the Study

If we establish a novel strategy for preventing development of AD by this skin moisturizer intervention for high-risk neonates, the prevalence of AD is expected to decrease and medical care costs will be reduced.

### Dissemination Plans

Main research results will be submitted to academic journals after the final analysis. The co-authors will be decided in accordance with the Uniform Requirements for Manuscripts Submitted to Biomedical Journals of the International Committee of Medical Journal Editors.

### Trial Status

Data are currently being collected. The protocol version number is 1.5 and the date is 1 April 2021. Recruiting participants began at 21 August 2020, and completed by September 2021.

## Ethics Statement

The studies involving human participants were reviewed and approved by the Accredited Clinical Research Review Committee of the National Center for Child Health and Development. Written informed consent to participate in this study was provided by the participants' legal guardian/next of kin.

## Abbreviations

AD: atopic dermatitis
CI: confidence interval
EASI: Eczema Area and Severity Index
IgE: immunoglobulin E
NCCHD: National Center for Child Health and Development
PAF: prevention of atopic dermatitis by applying Fam's Baby
POEM: patient-oriented eczema measure
RCT, randomized: controlled trial
TARC: thymus and activation-regulated chemokine.
